# Effects of robotic priming of bilateral arm training, mirror therapy, and impairment-oriented training on sensorimotor and daily functions in patients with chronic stroke: study protocol of a single-blind, randomized controlled trial

**DOI:** 10.1186/s13063-022-06498-0

**Published:** 2022-07-15

**Keywords:** Stroke, Upper extremity rehabilitation, Bilateral motor priming, Bilateral arm training, Mirror therapy, Impairment-oriented training, Randomized controlled trial

## Abstract

**Background:**

Combining robotic therapy (RT) with task-oriented therapy is an emerging strategy to facilitate motor relearning in stroke rehabilitation. This study protocol will compare novel rehabilitation regimens that use bilateral RT as a priming technique to augment two task-oriented therapies: mirror therapy (MT) and bilateral arm training (BAT) with a control intervention: RT combined with impairment-oriented training (IOT).

**Methods:**

This single-blind, randomized, comparative efficacy study will involve 96 participants with chronic stroke. Participants will be randomized into bilateral RT+MT, bilateral RT+BAT, and bilateral RT+IOT groups and receive 18 intervention sessions (90 min/day, 3 d/week for 6 weeks). The outcomes will include the Fugl-Meyer Assessment, Stroke Impact Scale version 3.0, Medical Research Council scale, Revised Nottingham Sensory Assessment, ABILHAND Questionnaire, and accelerometer and will be assessed at baseline, after treatment, and at the 3-month follow-up. Analysis of covariance and the chi-square automatic interaction detector method will be used to examine the comparative efficacy and predictors of outcome, respectively, after bilateral RT+MT, bilateral RT+BAT, and bilateral RT+IOT.

**Discussion:**

The findings are expected to contribute to the research and development of robotic devices, to update the evidence-based protocols in postacute stroke care programs, and to investigate the use of accelerometers for monitoring activity level in real-life situations, which may in turn promote home-based practice by the patients and their caregivers. Directions for further studies and empirical implications for clinical practice will be further discussed in upper-extremity rehabilitation after stroke.

**Trial registration:**

This trial was registered December 12, 2018, at www.clinicaltrials.gov (NCT03773653).

## Background

Stroke rehabilitation has evolved in recent decades to the formulation of promising therapies that are effective, including robotic therapy (RT) [1], mirror therapy (MT) [2], bilateral arm training (BAT) [3], and, more recently, hybrid therapy [4] that may involve concurrent or sequential combinations of monotherapies. Especially relevant for technology-based rehabilitation is the use of RT as a priming technique.

### Robotic therapy (RT)

RT features intensive, repetitive, and task-specific practice that incorporates crucial components of motor learning and neurorehabilitation. Several systematic reviews indicate that RT leads to improvements in upper-extremity (UE) motor strength, motor impairment, and motor function in stroke patients [5, 6]. However, the evidence for positive effects in participation in daily activities remains uncertain [7], especially in patients with chronic stroke [6]. Current RT protocols should be further modified, such as combining RT with contemporary approaches (e.g., BAT or MT), to intensify the treatment and enhance the benefits on broader aspects of functional outcomes pertaining to daily activities [8].

### Mirror therapy (MT)

MT is a rehabilitation therapy in which a mirror is placed between the arms so that the mirror box blocks the vision of the paretic arm, and the individual can only see the actual movements of the nonparetic arm and its mirror reflection. At the same time, the participant is encouraged to move the paretic arm along with the mirror reflection. Our published studies have demonstrated that MT could induce greater improvements in motor functions (e.g., decreased motor impairment), movement control strategies (e.g., reduced shoulder abduction during forward reaching), and daily activities (e.g., improved functional independency) compared with conventional occupational therapy [9, 10]. MT also ameliorated sensory deficits and reduced pain, which may be attributed to the referral of sensation and increased cortical somatosensory representations [11]. In addition to MT treatment alone, growing literature suggests that combining MT with an adjuvant therapy such as RT can further intensify the treatment effect [9].

### Bilateral arm therapy (BAT)

BAT involves simultaneous practice of the same activities with both UEs in a symmetrical or alternating pattern and has been used as an effective UE rehabilitation intervention for individuals with stroke at all levels of severity [12]. Bilateral symmetrical movements allow for activation of the undamaged hemisphere and promotion of neural plasticity to facilitate movement control of the affected extremity [13]. BAT has been shown to reduce motor impairment, increase grip strength, and improve motor control (e.g., increase temporal and spatial efficiency and decrease online error correction during reaching tasks) [3]. Recent systematic reviews indicate that the evidence is insufficient to conclude that BAT has a definitive effect compared with other treatments [14] and recommend more research with adequate experimental, dose-matched designs, and sufficient statistical power [15].

### Chi-square automatic interaction detector to identify predictors of treatment success

Compared with traditional statistical analysis, chi-square automatic interaction detector analysis can provide more robust information and uncover patterns that are usually undetected by traditional statistical methods [16]. Furthermore, chi-square automatic interaction detector analysis can generate a decision tree that splits participants into subgroups with similar characteristics based on the identified predictor variables. This type of decision tree analysis can not only classify responders but can also identify predictive variables that may be relevant to treatment success.

### Movement-based robotic priming

Motor priming in neurorehabilitation can be defined as a change in behavior on the basis of previous stimuli and is an emerging strategy to facilitate motor relearning [4]. As a therapeutic possibility, bilateral RT may be used as a bilateral priming technique in combination with different task-oriented therapies [17], such as MT and BAT, and may yield differential benefits. This project aims to investigate the comparative efficacy of these different combinatory approaches based on the tenet of bilateral movement practice approach. The primary goal of the comparative efficacy trial will be to explore the differential effects of the hybrid intervention of RT combined with MT and BAT on motor function, daily function, sensory, mobility, life quality, self-efficacy, and motor control strategy in stroke patients. The retention effects and possible delayed response of the interventions will be examined at 3-month follow-up. The second aim of this study will be to identify predictors of changes in quality of life after the interventions using the Chi-square Automatic Interaction Detector (CHAID) method

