### Statistical analyses

One-way analysis of variance and *χ*^2^ will be used to analyze differences in baseline characteristics and outcome measures among the three groups. Analysis of covariance will be conducted at the assessments, followed by a post hoc analysis using the Bonferroni test to identify the direction of the effects. Statistical significance will be set at 0.05 for all comparisons. We will use the “pretest” performance as a covariate to parcel out the possible confounding effects of differences in baseline performance. The group will be the independent variable and the posttest and follow-up test performance will be the dependent variable. The missing data will be adjusted based on the last observation carried forward (Herman, 2009). Partial eta squared (*η*^2^) will also be estimated to determine the group difference for each outcome measure. Predictors of intervention outcomes will be estimated with the chi-square automatic interaction detector method. Data analyses will be performed using the SPSS Statistics 18.0 software (IBM Corp, Armonk, NY).

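### Retention and delayed response at 3 months are stated aims, but no planned analysis estimates the change from posttest to follow-up, within arms or between arms.

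*Protocol article*

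**What the plan says.** The aims, under Movement-based robotic priming in the Background, state that "The retention effects and possible delayed response of the interventions will be examined at 3-month follow-up". The article defines neither term. The abstract confirms that the outcomes "will be assessed at baseline, after treatment, and at the 3-month follow-up", so both visits needed for a change after treatment are collected.

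Statistical analyses fixes the model. "Analysis of covariance will be conducted at the assessments, followed by a post hoc analysis using the Bonferroni test". Then: "The group will be the independent variable and the posttest and follow-up test performance will be the dependent variable". The pretest enters as a covariate: "We will use the “pretest” performance as a covariate to parcel out the possible confounding effects of differences in baseline performance". The level is common to all tests: "Statistical significance will be set at 0.05 for all comparisons". For missing values: "The missing data will be adjusted based on the last observation carried forward". Partial eta squared is to be reported for each outcome.

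The section names no visit factor, no group-by-visit term and no follow-up-minus-posttest contrast.

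**The concern.** In their ordinary sense, retention means that a gain present at posttest is still there at follow-up, and delayed response means that a gain appears after treatment has ended. Both describe what happens between the two later visits. The fixed model looks at each visit on its own, with group as the only factor.

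Two things follow. First, if every arm loses or gains the same amount after treatment, the group differences at posttest and at follow-up are identical and the shared movement never appears in the analysis. All three arms receive the same robotic priming, so shared gain and shared decay are plausible. Second, whether one arm keeps its gain better than another can only be inferred by setting the two visit-wise verdicts side by side. A difference that is significant at one visit and not at the other is weak evidence that anything changed. A fully retained effect could be reported as lost, or as delayed.

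**Working it through.** **1. What the plan estimates.** Write m1 and m2 for an arm's pretest-adjusted mean at posttest and follow-up. The plan estimates, for arms A and B, D1 = m1A − m1B and D2 = m2A − m2B. Retention or delayed response within an arm is m2 − m1. Differential retention is D2 − D1. Neither quantity is given an estimate, interval or test.

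**2. Shared loss.** If each arm loses the same amount L, then D2 = (m1A − L) − (m1B − L) = D1. The planned analysis gives the same expected group difference whatever L is.

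**3. The plan's own figure.** No figure is stated for this aim. The only one is the total of 96 (Sample size estimation). With the pilot eta squared of 0.114, f² = 0.114/0.886 = 0.129. A three-group F test then needs 78 completers for power 0.80, or 92 randomised at 15% dropout. So 96 is adequate for a three-group comparison at one visit and does not bear on this point.

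**4. Visit-wise verdicts against a direct test.** Assumptions not in the documents: FMA SD 12; 32 per arm, one pair of arms, no dropout; each test at two-sided 0.05 without Bonferroni adjustment; correlations pre–post, pre–follow-up and post–follow-up of 0.80, 0.75, 0.90 (base) or 0.90, 0.87, 0.95 (higher).

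Variances given pretest, with a, b, c the three correlations in that order:
- posttest 144(1 − a²), follow-up 144(1 − b²), covariance 144(c − ab);
- change = posttest + follow-up − 2 × covariance;
- SE of a group difference = SD × √(2/32) = SD × 0.25.

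| | Base | Higher |
|---|---|---|
| Posttest variance | 51.84 | 27.36 |
| Follow-up variance | 63.00 | 35.01 |
| Covariance | 43.20 | 24.05 |
| Change variance | 28.44 | 14.27 |
| Change SD | 5.33 | 3.78 |
| SE of between-arm difference in change | 1.33 | 0.94 |

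Simulated ANCOVAs on these inputs give:

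| | Base | Higher |
|---|---|---|
| True difference 5 then 5: verdicts disagree | 20% | 8% |
| of which significant at posttest only | 14% | 6% |
| of which significant at follow-up only | 6% | 1% |
| True difference 5 then 5: direct test rejects | 5% | 5% |
| True difference 5 then 2: direct test detects the fall | 60% | 88% |
| True difference 5 then 2: significant at posttest, not at follow-up | 61% | 70% |

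With 27 per arm (15% dropout from 32), disagreement under full retention is 22% and about 11% to 12%.

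**5. A second route, tied to the protocol's effect size.** A three-group simulation with eta squared 0.114 at both visits and an assumed residual correlation between visits of 0.5 to 0.9 gives disagreement in 7% to 16% of trials with 32 per arm and 10% to 23% with 27 per arm. The direct test rejects in about 5%.

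**6. Carried-forward values.** A patient without follow-up gets the posttest value, so the change is 0. If such patients would have changed like the rest, 10% to 15% dropout shrinks an arm's change by the same percentage. A 3-point loss would show as 3 × 0.90 = 2.70 to 3 × 0.85 = 2.55, which leans towards retained.

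**The case against.** The strongest defence is that the aim is already met. The primary goal is comparative, the sentence speaks of examination at follow-up, and the follow-up ANCOVA with partial eta squared does estimate the baseline-adjusted difference at 3 months. On that reading, a group difference that persists or emerges late is examined. This stands in part: a reader might infer that nothing about retention is estimated at all, and the documents do not support that. Nor are groups tested against their own pretest; they are compared with each other, with the pretest as covariate.

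A reader might also infer that the article adopts the rule of comparing two p-values. It does not say so. It leaves retention undefined, and that comparison is simply what its planned tests allow. The 8% to 20% measures the hazard of that route, not of a written rule.

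The direct test has limits too. For a true fall from 5 to 2 points, the side-by-side reading shows the expected pattern about as often at the base correlations (61% against 60%). The direct test also misses the fall in about 40% of trials there, so a non-significant change would not establish retention. Its advantage is an estimate with an interval and a controlled false-positive rate.

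Finally, an analysis plan that is not shown might contain the contrast. But the article does more than leave the matter open: it names factor, covariate, outcomes, post hoc test and missing-data rule, and the model so fixed does not address the posttest-to-follow-up change.

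**Conclusion.** The aim and the fixed analysis do not match. The change from posttest to follow-up is neither estimated nor tested, within arms or between arms, and a change common to all arms cannot be seen. This holds whatever the numbers are. The size of the risk in judging differential retention from visit-wise significance (about 8% to 20% discordant verdicts under full retention, against 5% for a direct test) rests on the assumed SD, difference and correlations.

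A reader might conclude that the trial's main result is in doubt. It is not: this point does not undermine the group comparison at posttest or at follow-up. Only the conclusion on retention and delayed response is at risk. The plan should be changed, because the repair uses data already collected and lets the trial answer a question that it sets itself.

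**What to change.** Keep the visit-wise ANCOVA for the comparative aim. Add to Statistical analyses:

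- A definition of retention and of delayed response in terms of the posttest-to-follow-up change.
- A repeated-measures mixed model with posttest and follow-up as outcomes, pretest as covariate, and group, visit and group-by-visit.
- The posttest-to-follow-up change with 95% CI for each arm, and the between-arm differences in that change with 95% CI.
- For this contrast, the observed data rather than last observation carried forward. The model then assumes that missingness depends only on observed data.
- A statement that retention will be judged from the estimate and its interval, not from significance at one visit only and not from a non-significant change.

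The cost is wording and slightly more analysis work. No visit or measurement is added, and the trial was still recruiting when the article was submitted. Precision will be limited: with the SEs above, a between-arm 95% interval is about ±2.7 points (2.0 × 1.33) or ±1.9 points (2.0 × 0.94) with 32 per arm, and wider after dropout. The report should say so.

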### Sample size estimation

No published research to date has compared the effects of bilateral RT+MT, RT+BAT, and RT+impairment-oriented training (IOT). Thus, the sample size required for this project was calculated and estimated based on our published studies [8, 21, 22].

In a previous study, we randomized 21 stroke patients to two treatments: RT+task-oriented training and RT+IOT [21]. Between-group analyses revealed small to large effects on the FMA (*p* = 0.01, *η*^2^ = 0.43), Stroke Impact Scale (*p* = 0.046, *η*^2^ = 0.29), and Medical Research Council scale (*p* = 0.98, *η*^2^ < 0.01), respectively.

An additional 21 stroke patients were randomized to receive RT+BAT or RT [8]. Between-group analyses revealed small to large effects on the FMA (*p* = 0.82, *η*^2^ = 0.003) and Goal Attainment Scale total scores (*p* > 0.01, *η*^2^ = 0.633). We randomized 23 stroke patients to two treatment groups: MT and BAT [22]. Between-group analyses revealed small to large effects on the FMA (*p* = 0.67, *η*^2^ = 0.009) and Stroke Impact Scale Version 3.0 total scores (*p* = 0.02, *η*^2^ = 0.165), respectively.

In addition, we used the pilot data of three groups for the FMA proximal UE score (*p* = 0.051, *η*^2^ = .114) to calculate sample size. In light of our previous findings [8, 21, 22], we estimate that to achieve a statistical power of 0.80 with a two-sided type I error of 0.05 and with an estimated dropout rate of 10% to 15% at the 3-month follow-up, a total sample size of 96 with 32 subjects for each group will be sufficient.

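### Aim 2 searches for predictors of a change score with CHAID at a flat 0.05, so it will tend to select baseline quality of life by regression to the mean and has no stated allowance for the number of candidate predictors

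*Protocol article*

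**What the plan says.** The protocol article describes the tree analysis in three places, and each gives a different outcome.

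- Movement-based robotic priming, second aim: to "identify predictors of changes in quality of life after the interventions using the Chi-square Automatic Interaction Detector (CHAID) method". The outcome is change in quality of life. The quality-of-life instrument among the outcome measures is the Stroke Impact Scale 3.0.
- Statistical analyses: "Predictors of intervention outcomes will be estimated with the chi-square automatic interaction detector method". The outcome is unspecified.
- The background section on CHAID: "This type of decision tree analysis can not only classify responders but can also identify predictive variables that may be relevant to treatment success". This implies a responder classification. The same section says that the method "can provide more robust information and uncover patterns that are usually undetected by traditional statistical methods".

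On error control, Statistical analyses states "Statistical significance will be set at 0.05 for all comparisons". The Bonferroni step belongs to the analysis of covariance, which is "followed by a post hoc analysis using the Bonferroni test to identify the direction of the effects". The pretest covariate is also described only there. The sample size is justified for the group comparison ("statistical power of 0.80 with a two-sided type I error of 0.05", hence "a total sample size of 96 with 32 subjects for each group will be sufficient"). The aim is not labelled exploratory.

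**The concern.** Two separate mechanisms can put wrong variables into the tree.

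The first is systematic. Change is posttest minus pretest, so the pretest enters its own outcome with a minus sign. Patients with low baseline scores tend to gain and those with high scores tend to lose, whatever the therapy does. A tree on raw change can therefore report baseline quality of life, or something related to it, as a predictor of benefit. The plan already adjusts for pretest in the analysis of covariance but does not carry this over to aim 2.

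The second is chance. CHAID picks the predictor with the smallest p-value. Its internal Bonferroni factor accounts for the ways of merging categories within that predictor, not for how many predictors competed. At 0.05 per predictor, the chance of a false split grows with the candidate list.

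At stake is whether the variables reported under aim 2 say anything about who improves. The primary group comparison is not affected.

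**Working it through.** **Inputs from the article.** N = 96, 32 per arm; level 0.05; dropout 10% to 15%, which leaves about 86 to 82 patients with follow-up data; last observation carried forward, so dropouts may stay in the tree; pilot eta squared 0.114.

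**Assumed, because the article does not give them.** Number of candidates k = 5, 10, 20; pre-post correlation r = 0.6 and 0.8; tree depth 3; parent nodes of at least 10 and child nodes of at least 5.

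**1. The plan's own figure.** f = sqrt(0.114/0.886) = 0.359. A three-group F test at 0.05 with power 0.80 needs 78 evaluable patients. Dividing by (1 - dropout) gives 78/0.90 = 87 and 78/0.85 = 92, or 93 in equal arms. With 81 evaluable (96 less 15%), power is 0.817. So 96 is adequate for the group comparison on this effect size, and slightly generous. No size or error rate is stated for the tree.

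**2. Baseline against change.** With equal pre and post SDs, corr(baseline, change) = -sqrt((1 - r)/2).

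- r = 0.6: -sqrt(0.20) = -0.45
- r = 0.8: -sqrt(0.10) = -0.32

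Simulated CHAID root test, N = 96, predictors in quartiles, 1,000 runs per value of r:

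| Candidate | Raw change, r = 0.6 | Raw change, r = 0.8 | Baseline-adjusted, r = 0.6 | Baseline-adjusted, r = 0.8 |
|---|---|---|---|---|
| Baseline score | 97% | 75% | 1% | 1% |
| Variable correlated 0.5 with baseline score only | 44% | 25% | 4% | 4% |

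The baseline-adjusted target is the residual of posttest regressed on pretest.

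**3. Number of candidates.** For independent null predictors, each tested at 0.05, P(at least one false) = 1 - 0.95^k. Full CHAID trees were also simulated for a continuous target: adjacent-category merging at 0.05, within-predictor Bonferroni, 1,500 runs per setting, four sets of predictor types, N = 82 and 96.

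| k | Formula | Simulated at 0.05 | Simulated at 0.05/k |
|---|---|---|---|
| 5 | 23% | 18-24% | 4-6% |
| 10 | 40% | 34-44% | 5-6% |
| 20 | 64% | 56-68% | 4-7% |

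By formula, 0.05/k gives 4.9% for each k. Sample size makes little difference: with mixed predictor types and k = 10, the rate is 39.6% at N = 96 and 40.7% at N = 82. The simulation error at 40% is about sqrt(0.4 x 0.6/1500) = 1.3 percentage points.

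**The case against.** The strongest reply is that this is a condensed article giving one sentence to a secondary analysis. The candidate list, split level, tree settings and validation may all stand in a fuller document. That reply disposes of several tempting readings.

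- A reader might infer that no validation is planned. The article is silent on this and does not say there will be none.
- A reader might infer that the tree pools the arms and so can find only prognostic factors. Pooling is stated nowhere. The abstract speaks of predictors of outcome after each of the three regimens, which is compatible with separate trees or with group as a candidate. The aim itself can be read as a prognostic question.
- A reader might blame the small sample for false predictors. The false-split rate is nearly the same at 82 and 96 patients. A small sample limits power and the stability of splits, which is a different matter.
- A reader might say that false predictors will be frequent, full stop. How frequent depends on a number that the article does not give.

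It can also be said that change appears only in the aim, that baseline quality of life is not named as a candidate, and that the 0.05 sentence may have been written with the group comparisons in mind. Each is fair. But the aim is the only place that names the quality-of-life outcome, and 0.05 is the only level given. A responder definition based on a change threshold would bring regression to the mean back in.

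One technical limit also stands. The 44% and 25% apply to a variable linked to the observed pretest score that carries no further information about the posttest. A variable linked to the patient's stable underlying level need not correlate with change at all. The result for the baseline score itself does not need this assumption.

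**Conclusion.** The point holds in a limited form, as a matter of what the article fixes: a change outcome for the tree, one flat 0.05 level, and baseline adjustment and Bonferroni described only for the analysis of covariance.

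The change score is the firmer half. With equal SDs, the negative correlation exists for any r below 1; only its size depends on r. It would shrink or vanish if the posttest SD were enough larger than the pretest SD. Whether the baseline score is actually selected depends on its being offered as a candidate.

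The multiplicity half is conditional on k: about 1 trial in 5 with a false predictor at 5 candidates, 2 in 5 at 10 and 3 in 5 at 20, for independent null candidates. Even the low end is about four times the nominal 5%.

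The three descriptions of the outcome also disagree and need reconciling. This is a worthwhile correction to a secondary aim. It gives no ground for abandoning CHAID.

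**What to change.** Keep CHAID, with these changes:

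1. Label aim 2 exploratory.
2. Use as target the posttest Stroke Impact Scale adjusted for its pretest, for example the residual from regressing posttest on pretest, in place of raw change.
3. Fix a short list of candidate predictors in advance and include treatment group in it.
4. Split at 0.05 divided by the number of candidates, in addition to CHAID's within-predictor correction.
5. Report cross-validated error alongside the tree.
6. State one outcome for the tree and use it in the background section on CHAID, the second aim and Statistical analyses.

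Replacing CHAID by a covariance model with group-by-factor terms is not needed. It would change the question from prognosis to effect modification and bring its own multiplicity.

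The cost is fewer detected splits, because the stricter level also lowers the chance of finding real predictors, and some extra programming. The pretest is already collected, and neither sample size nor patient procedures change.
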